### Randomisation

Randomisation is carried out within 24 hours of the baseline interview (t1) by a third party (Addenbrooke's clinical trials' team) sequentially opening sealed opaque envelopes containing the random group allocation previously generated using a computer programme by the study statistician (University of Cambridge). The envelopes were set up by an administrator at University of Cambridge. Patients are allocated to the fast track group or waiting list group with an equal 1:1 allocation ratio using the method of stratified randomisation, with disease group (malignant, non-malignant) as the single stratifier.

Patients are informed of the outcome of randomisation by the clinical trials' team, by telephone. BIS is then notified of the outcome of randomisation by the clinical trials' team (by secure email) in order that the service can book the first appointment with the patient in-line with the study protocols. The researcher is then notified that randomisation has occurred, and that the patient and service have been informed, but not the outcome of the randomisation. The purpose and need for single blinding is explained to patients and carers at the recruitment visit and they are reminded at the start of each subsequent blinded interview to try not to let the researcher know their group allocation. In addition, all data are handled using study identity numbers; group allocation identifiers will only be added at the analysis stage. A detailed description and discussion of single-blinding, piloted at Phase II, has been given elsewhere [20].

### Data collection interviews

Face to face mixed method interviews are conducted at a time and place convenient to the participant (usually their home). Careful attention is paid to both patient and carer need, in terms of fatigue. With permission, interviews are audio-recorded for transcription. Field notes are recorded after each interview. Interviews are conducted by one of three researchers: an experienced palliative care researcher (nursing background) or one of two sequentially employed researchers (nursing and psychology backgrounds respectively) who have been given full training (external in-depth interviewing course, internal training with the interview schedule and ongoing supervision). The researchers are allocated caseloads so that the same researcher conducts all interviews for patient X, their carer, their referrer and their non-referring health care professional.

### Measurement points

The data collection points (interviews) are outlined in Figures 1 and 2. Baseline interviews are collected for all respondents, regardless of diagnostic group, at t1, prior to randomisation.

For patients with non-malignant conditions and their carers, t2 occurs two weeks post t1 and the commencement of BIS (fast track group) or the entering of the waiting list (waiting list group), and t3 occurs four weeks post commencing BIS (fast track group) or the entering of the waiting list (waiting list group). The waiting list group have a t4 interview scheduled two weeks post their commencement of BIS (six weeks from t1). T5 occurs eight weeks after t1 (i.e. on discharge from BIS for the waiting list group or four weeks from discharge for fast track group). This model was successfully piloted at Phase II [20]. Therefore for those randomised to the fast track group, t2 and t3 represent mid-point and completion of the BIS intervention, for comparison with these same time-points in the contemporaneous control condition for those randomised to the waiting list group.

Due to the shorter time frame of the service model for patients with malignancies, there are no t2 or t4 interviews for patients or their carers in this group. Instead, t3 is conducted 2 weeks post t1 i.e. on discharge from BIS for the fast track group or just prior to commencement of BIS for the waiting list group. T5 then occurs four weeks after t1 (i.e. on discharge from BIS for the waiting list group or two weeks from discharge for fast track group). Therefore t3 is the time-point marking completion of the BIS intervention for those randomised to the fast track group, and the control condition in those randomised to the waiting list group.

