**Figure 2 F2:**
[figure not shown]
**BIS Phase III measurement point flow chart - malignant conditions**. shaded area = intervention

**Table 1 T1:** Service model for the Breathlessness Intervention Service (BIS) at Addenbrooke's Hospital, Cambridge University Hospitals NHS Foundation Trust (March 2008)

Disease group course:	Non-malignant (nm) course	Malignant (m) course
Examples:	e.g. COPD, heart failure, neurological disorders	e.g. all cancers, UIP

Referral:	Post, fax, electronic	Post, fax, electronic

Assessment lead:	Clinical Specialist Physiotherapist or Clinical Specialist Occupational Therapist	Medical Consultant (i.e. sees a doctor earlier in the intervention than non-malignant patients)

BIS team:	Clinical Specialist Occupational Therapist Clinical Specialist Physiotherapist Medical Consultant	Medical Consultant Clinical Specialist Occupational Therapist Clinical Specialist Physiotherapist

Medical assessment:	May be required	Always required (review of pharmacological management at 1^st ^visit)

First appointment:	Maximum wait of 3 weeks for first appointment	Maximum wait of 1 week for first appointment

Range of face-to-face visits:	2-3	1 (with primary care professional)

Average no. of telephone contacts (with patient/primary care staff):	3	2

Ratio of face-to-face to telephone:	1:1	2:1

Average length of service contact:	4 weeks + 16 week follow up (from 1^st ^assessment) post any pulmonary rehab/other referral	2 weeks + 6 week follow up (from 1^st ^assessment) post any pulmonary rehab/other referral

Service outcome measures collected at first assessment:	• modified BORG at rest, self-reported, on exertion and on completion of exercise test • anxiety due to breathlessness at rest, self reported, on exertion and on completion of exercise test • physiological measures e.g. oxygen saturation, heart rate	• modified BORG at rest, self-reported, on exertion and on completion of exercise test • anxiety due to breathlessness at rest, self reported, on exertion and on completion of exercise test (if acceptable) • physiological measures e.g. oxygen saturation, heart rate

Non-pharmacological interventions:	1^st ^stage of intervention	More likely to be concurrent with pharmacological interventions

Pharmacological interventions:	2^nd ^stage of intervention	More likely to be concurrent with non-pharmacological interventions

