Documentation:	→ individualised patient plan → summary to patient of outpatient consultation with medical consultant → discharge summary to referrer with copies to GP, specialist services the patient was already in contact with (e.g. respiratory physicians), other involved health care professionals (e.g. district nurses, nursing home care staff)	→ individualised patient plan → summary to patient of outpatient consultation with medical consultant →discharge summary to referrer with copies to GP, specialist services the patient was already in contact with (e.g. respiratory physicians), other involved health care professionals (e.g. district nurses, nursing home care staff) → supplementary medical letters more common

Referrals:	→ Pulmonary rehabilitation → Specialist dietetic → Specialist psychological services → Hospice day services → other specialist assessment → Cardiac rehabilitation → other rehab services (n.b. these services usually have a wait time)	→ Palliative care specialist service (n.b. rapid access available) → Specialist psychological services → Hospice day services → other specialist assessment

While understanding that it is not possible or desirable to standardize all aspects of the Breathlessness Intervention Service (BIS) for individual patients, we have established a service model with a minimum set of core interventions. The norm is for consultations to occur in the patient's own home (with clinically reasoned variance)

LTOT = long term oxygen therapy

SBOT = short burst oxygen therapy

Based on methods piloted at Phase II [20,21], consented patients are randomised either to a 'fast-track' group where they receive BIS immediately or to a waiting list group (control condition) where they receive the intervention after a defined period on a waiting list during which time they receive standard care. The advantage of a fast-track design is that it has the strength of a RCT, but with greater acceptability as all patients receive the intervention. Due to the palliative status of the patients referred to BIS, and the existence of BIS prior to this proposed RCT, a traditional intervention and control group design (where the control group would be denied access to the service) would be unethical and unacceptable [22]. This alternative fast-track design proved highly acceptable at Phase II [20].

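### Non-malignant t3, the primary time point, is counted from BIS start in the fast-track arm but from waiting-list entry in the control arm; the stated schedule is consistent only if BIS starts at t1

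*Protocol article*

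**What the plan says.** All references are to the protocol article.

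- **Measurement points, non-malignant.** For t2: "t2 occurs two weeks post t1 and the commencement of BIS (fast track group) or the entering of the waiting list (waiting list group". For t3: "t3 occurs four weeks post commencing BIS (fast track group) or the entering of the waiting list (waiting list group". For t4, in the waiting-list arm only: "two weeks post their commencement of BIS (six weeks from t1". For t5: "T5 occurs eight weeks after t1", which the text equates with discharge in the waiting-list arm and with four weeks after discharge in the fast-track arm. The section says that fast-track t2 and t3 are to be compared with the same time points in a concurrent control.
- **Measurement points, malignant.** "t3 is conducted 2 weeks post t1 i.e. on discharge from BIS for the fast track group". T5 is four weeks after t1, equated with two weeks after fast-track discharge.
- **Design.** Fast-track patients are in the group "where they receive BIS immediately or to a waiting list group". The intervention lasts four weeks (non-malignant) or two weeks (malignant).
- **Randomisation.** Allocation takes place within 24 hours of t1. The patient is then telephoned, BIS is emailed, and the service books the first appointment in accordance with the study protocols. The researcher is not told the allocation.
- **Table 1 (service model, March 2008).** Non-malignant: "Maximum wait of 3 weeks for first appointment". Malignant: "Maximum wait of 1 week for first appointment".
- **Analysis.** The effectiveness questions are answered by comparing the arms at t3, adjusted for baseline; t2 supports this in the non-malignant group.

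**The concern.** The t3 contrast is the randomised comparison on which the trial rests. If one arm's t3 is counted from an event that happens some time after allocation and the other's from entry to the list, the arms are measured after unequal elapsed time. In progressive disease this matters in two ways. The fast-track arm has longer in which to deteriorate, or to recover by other means, and its patients must remain alive and in the study for longer to be measured. The direction of the resulting bias is not known in advance.

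There is also a blinding issue. One researcher conducts all of a patient's interviews, including t1. If t3 is set from BIS start, an interview visibly later than four weeks after t1 hints at the fast-track arm. The primary outcome is a self-rating collected in that interview.

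If t3 is instead held at a fixed interval from t1, elapsed time is equal, but t3 may come before the end of the BIS course in some fast-track patients. The description of t3 as marking completion of BIS then no longer holds exactly.

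**Working it through.** **Inputs.** Course length is 4 weeks (non-malignant) or 2 weeks (malignant), from Design. The t1-based times of t4 and t5, and of malignant t3, come from Measurement points. SD 2.5, difference 2 points and 26 per arm per disease group come from Sample size. Let w be the number of weeks from t1 to fast-track BIS start; the article gives no value. I assume that list entry occurs at randomisation, so control t3 is between 4 and 4 + 1/7 weeks after t1, shown as 4 below.

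**Step 1: the plan's own figure.** The planned sample size reproduces. A two-sample t-test with difference 2, SD 2.5, two-sided 5% and 80% power needs 25.5 per arm, rounded up to 26. Power at 26 is 80.7%, and 26 × 2 arms × 2 disease groups = 104. The point below concerns timing, not this number.

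**Step 2: what the schedule implies.**
- Waiting-list BIS start, from t4: 6 − 2 = 4 weeks after t1.
- Fast-track discharge, from t5: 8 − 4 = 4 weeks after t1. With a four-week course, fast-track BIS start is 4 − 4 = 0 weeks after t1.
- Malignant fast-track discharge, from t5: 4 − 2 = 2 weeks after t1. With a two-week course, start is again 2 − 2 = 0.

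Both sub-protocols are exact only at w = 0. Randomisation, notification and booking all follow t1, so w is in practice above zero.

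**Step 3: non-malignant, as a function of w.** If t3 is counted from BIS start, fast-track t3 is at 4 + w. Discharge is also at 4 + w, so t5 falls 8 − (4 + w) = 4 − w weeks after discharge. If t3 is instead counted from t1, the elapsed share of the course is (4 − w)/4.

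| w (weeks) | Fast-track t3 | Control t3 | t5 minus discharge (stated: 4) | Share of course if t3 = t1 + 4 |
|---|---|---|---|---|
| 0 | 4 | 4 | 4 | 100% |
| 1/7 (1 day) | 4.14 | 4 | 3.86 | 96% |
| 1 | 5 | 4 | 3 | 75% |
| 3 | 7 | 4 | 1 | 25% |

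For t2, two weeks after t1 is 2 − w weeks after BIS start, so its two anchors also separate for any w above zero.

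**Step 4: malignant.** t3 is t1 + 2 weeks in both arms, so elapsed time is equal. The elapsed share of the course is (2 − w)/2, and t5 falls 4 − (2 + w) = 2 − w weeks after discharge.

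| w (weeks) | Share of course at t3 | t5 minus discharge (stated: 2) |
|---|---|---|
| 0 | 100% | 2 |
| 1/7 (1 day) | 93% | 1.86 |
| 3/7 (3 days) | 79% | 1.57 |
| 1 | 50% | 1 |

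The rows at w = 3 (non-malignant) and w = 1 (malignant) take the Table 1 maxima as if they ran from t1, which the article does not say.

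**Step 5: illustration only.** Suppose the 2-point effect built up in proportion to elapsed course, with 26 per arm, SD 2.5 and no gain from baseline adjustment. A share of 93% gives 1.86 points and 75% power; 79% gives 1.57 points and 60%; 75% gives 1.5 points and 56%; 50% gives 1.0 point and 29%; 25% gives 0.5 point and 11%. The article supports neither the proportional build-up nor any particular w.

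**The case against.** The strongest reply is that Measurement points, read as a whole, describes one common schedule. The t2 sentence treats t1, BIS start and list entry as the same moment, t4 and t5 are placed from t1, and the declared aim is a concurrent comparison at matching times. Design says that fast-track patients receive BIS immediately, and booking follows the study protocols. On this view the t3 sentence is loose wording, and Figures 1 and 2 (not shown here) or the full protocol may state the origin and windows.

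Much of this stands. The authors evidently mean the events to coincide, and the absence of visit windows from an article is no fault. But the t3 sentence is not missing detail: it is a stated rule with an arm-specific starting event, at the primary time point, and the sequence under Randomisation does not allow the events to coincide exactly.

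Four stronger readings are tempting, and the article does not support them:

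- **Different clocks throughout the trial.** Malignant t3 is two weeks from t1 in both arms. The unequal clock is confined to the non-malignant sub-protocol.
- **Table 1 contradicts the schedule.** Its waits are maxima of the service model, with no stated starting event. They might run from referral, in which case part of the wait is used before t1, and a maximum does not exclude a prompt start. They are at most an upper bound on w.
- **The trial is underpowered.** The figures in Step 5 rest on assumed waits and linear accrual. For malignant patients Table 1 points away from linear accrual: one face-to-face visit, pharmacological review at the first visit, and the two stages of intervention likely to run concurrently. Elapsed weeks are therefore not the same as the share of BIS delivered.
- **The single blind is defeated.** Allocation is withheld from the researcher, and the times stated from t1 can be scheduled without it. A cue arises only if t3 is actually set from BIS start.

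**Conclusion.** The point holds for the non-malignant t3 rule. Its two anchors put fast-track t3 at 4 + w weeks from t1 against about 4 in control, contrary to the section's own aim, and create a possible cue to allocation. In both sub-protocols the statements that link t3 or t5 to fast-track discharge are exact only at w = 0; in the malignant sub-protocol this is the only defect.

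The size depends on w, which the article does not give. At a gap of one day the non-malignant difference is 0.14 week; at one week it is 5 against 4. The figure of 7 against 4 is a bound that needs the Table 1 maximum to run from t1, and should not be read as what the plan prescribes. Unequal timing is thus a consequence of any real gap, not a stated intention, and no loss of power is established. It still deserves correction because it concerns when the primary outcome is measured and is cheap to settle.

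**What to change.** 1. Define t2, t3 and t5 in each sub-protocol as the same interval from t1 (or from randomisation) in both arms, with one common window, and drop BIS start as the anchor for t3. This equalises elapsed time and removes the scheduling cue.
2. Record the date of first BIS contact and report, by disease group, how far the BIS course had progressed at t3. Describe t3 as the planned end of the intervention rather than as discharge, and reword the t5 statements about weeks from discharge accordingly.
3. Reconcile Table 1, Design, Randomisation and Measurement points on when fast-track BIS begins, including what the Table 1 waits run from. The clinical team decides which text changes.

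The cost is protocol wording and an interview-scheduling rule, with no extra patients. The downside is that some fast-track patients will be measured before their last BIS contact, which may slightly reduce the intention-to-treat effect. The reduction stays small only if the gap is short relative to the course, which is why steps 2 and 3 belong with step 1.

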### Sample size

Sample size was calculated using a power calculation, with the potential effect size and standard deviation informed by the existing literature and our Phase II trial [20]. The estimated standard deviation of the primary outcome measure is 2.5. In order to detect a 2-point difference in mean outcome between groups (equivalent to 0.8 sd effect size) with 80% power using a two-sided t-test at the 5% level of significance, it is necessary to analyse 26 patients per arm per disease group (trial) followed up with a primary outcome (total 104 patients). Therefore we propose to recruit a minimum of 120 patients, 60 per disease group, to ensure adequate power, effect size and allowance for attrition. Additionally, an adjustment for baseline in the analysis will improve the precision of the estimated intervention effect.

### Outcome measures

Table 3 outlines the baseline and outcome measures selected following a review of the literature and, to avoid duplication, a review of measures used by the clinical service [23-31]. Baseline characteristics and outcomes include patients' breathlessness, patient and carer distress due to breathlessness, patient and carer quality of life, patient and carer anxiety, other service use, caregiver burden, and patient and carer expectations of and satisfaction with BIS. The primary outcome measure is 'distress due to breathlessness' measured using a Numerical Rating Scale (NRS; 0-10).

**Table 3 T3:** Patient and carer baseline and outcome measures for BIS Phase III RCT

Baseline characteristic/outcome	Instrument/measure
**PATIENT**	

Patient breathlessness	Numerical Rating Scale (NRS) for breathlessness [23] at worst/average over last 24 hours/now; modified Borg [24] at rest and on exertion & identification of activity that makes breathlessness worst

Patient distress due to breathlessness (primary outcome measure)	NRS for distress due to breathlessness (after Corner et al 1995 [25])

Patient quality of life	Chronic Respiratory Questionnaire [26] EQ-5D [27]

Patient anxiety & depression	Hospital Anxiety and Depression Scale [28]

Patient use of other services	CSRI [29]

Patient social functioning	No. of times patient goes out of the house (weekly average since last interview)

Patient experience of breathlessness & expectations of BIS/satisfaction & outcome of BIS	Brief qualitative interview: t1 - experience of breathlessness & expectations of BIS t3/t5 - satisfaction and outcome of BIS

**CARER**	

Carer's assessment of patient's breathlessness	Numerical Rating Scale (NRS) for breathlessness [23] at worst/average over last 24 hours/now; modified Borg [24] at rest and on exertion & identification of activity that makes breathlessness worst

Carer distress due to patient's breathlessness	NRS adapted for carer for distress to carer due to patient's breathlessness

Carer quality of life	EQ-5D [27]

Carer anxiety & depression	Hospital Anxiety and Depression Scale [28]

Carer's social functioning	No. of times carer goes out of the house (weekly average since last interview)

Caregiver burden	Burden Interview [30] Caregiver Appraisal Scale [31]

Carer experience of breathlessness & expectations of BIS/satisfaction & outcome of BIS	Brief qualitative interview: t1 - experience of breathlessness & expectations of BIS t3/t5 - satisfaction and outcome of BIS

At t1, prior to quantitative data collection, a brief qualitative interview is conducted to identify respondents' experiences of breathlessness, or caring for someone who is breathless, and their expectations of BIS. Following receipt of BIS (t3 for fast track group; t4 and t5 for waiting list group) and after quantitative data collection, a brief qualitative interview is conducted to identify respondents' experiences of and satisfaction with BIS. The resulting interview schedule is therefore both quantitative and qualitative at each measurement point except t2.

In addition, brief semi-structured interviews are conducted with patients' referrers two weeks after the referrer's first patient is discharged from BIS. This allows time for receipt of discharge documentation. Referrers are only approached for interview after their first referral to the service within the RCT; they are assured that they will not be asked for interview after every referral.

For patients with malignant conditions, a second health care professional interview is sought with a non-referring health care professional (identified by the clinical team) to capture potential knock-on effects (positive or negative) of a BIS referral on other health care professionals.

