### Recruitment

A Patient Information Sheet is sent by first class post to eligible patients inviting participation in the trial. On the sub-protocol for patients with non-malignant conditions a second mailing is sent if there is no response within a week. On the sub-protocol for patients with malignancies a BIS clinician conducts a telephone follow-up if there is no response within a week; this clarifies that the patient has received a recruitment pack and establishes whether or not they would like to participate in the trial. If the patient (from either sub-protocol) refuses trial participation, or there is still no response, the service arranges to see the patient in the usual way and they are not recruited to the trial. If the patient responds positively to a recruitment letter a researcher contacts them to arrange to visit and explain the study in more detail, answer any questions, obtain informed consent, conduct the baseline interview (t1) and identify their lay carer.

If their lay carer is present at the patient's t1 then they are directly invited to participate in the study. If they are willing then the researcher answers any questions, obtains informed consent and conducts the carer baseline interview (t1). Where possible, carers are interviewed separately from patients as this was found to be important in the Phase I of the evaluation [3]. If the lay carer is not present then a recruitment pack (similar to that for the patient) is either left for them with the patient, or posted to them, depending on circumstances. They are then approached in the same way as for patients.

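### At t3 the interview about BIS, or its absence, can reveal a dyad's allocation to its single blinded researcher before the second member's quantitative outcomes are collected

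*Protocol article*

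**What the plan says.** The relevant provisions of the protocol article sit in five sections.

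- **Randomisation.** The researcher learns that randomisation has taken place, "but not the outcome of the randomisation". Patients and carers are "reminded at the start of each subsequent blinded interview to try not to let the researcher know their group allocation". Allocation identifiers are added to the data only at the analysis stage.
- **Data collection interviews.** Caseloads are arranged so that "the same researcher conducts all interviews for patient X, their carer, their referrer and their non-referring health care professional".
- **Recruitment.** "Where possible, carers are interviewed separately from patients as this was found to be important in the Phase I of the evaluation". This sentence belongs to the description of the baseline visit.
- **Outcome measures, text below Table 3.** The timing of the interview about BIS is given by arm: "Following receipt of BIS (t3 for fast track group; t4 and t5 for waiting list group) and after quantitative data collection". Its content is experience of the service and satisfaction with it. The next sentence adds: "The resulting interview schedule is therefore both quantitative and qualitative at each measurement point except t2".
- **Analysis.** Effectiveness, including patient and carer distress, is judged by comparing the arms at t3, adjusted for baseline.

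**The concern.** Single-blinding of the researcher is presented as a distinctive feature of this trial. Outcomes are collected face to face, so it is the design's guard against an interviewer influencing ratings. The article protects the blind by asking the quantitative questions before the qualitative ones. Read as a rule for each respondent, this keeps the BIS discussion away from that respondent's own ratings. Researchers, however, are assigned by dyad. Once the first member of a dyad has finished the t3 schedule, the researcher has either discussed experience of BIS or has had no such discussion, and either one points to the arm. The second member's t3 quantitative measures would then be taken by someone who knows the allocation.

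At stake is interviewer influence on the t3 contrast: on carer outcomes if the patient is seen first, and on the primary outcome if the carer is seen first.

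**Working it through.** **Setting the provisions together**

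1. The researcher should be blind when t3 quantitative data are collected (Randomisation).
2. The same researcher sees patient and carer (Data collection interviews).
3. Carers share the t3 time point with patients (Measurement points).
4. At t3 the fast-track group has received BIS and the waiting-list group has not. The interview about BIS is therefore tied to t3 for fast track and to t4 and t5 for waiting list (Outcome measures).
5. Nothing in the article holds that interview back until both dyad members have given their quantitative data, and nothing gives it to another researcher.
6. The reminder to participants not to disclose allocation cannot help when the schedule itself asks about BIS. Withholding identifiers until analysis protects data handling, not the interview.

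So in any dyad seen in sequence with full schedules, the second member is interviewed by an informed researcher. This applies in both arms.

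**Does another reading of the schedule remove the problem?** The sentence making every point except t2 both quantitative and qualitative, and the t3/t5 entry in Table 3, do not separate the arms. If waiting-list respondents also had a qualitative section at t3, they could not describe a service they had not received. Allocation would still be disclosed.

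**Which outcomes are exposed**

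- Patient first: carer t3 outcomes (distress, HADS, EQ-5D, burden). The primary outcome is protected.
- Carer first: the patient's t3 outcomes, including the primary distress rating.
- No participating carer: none.

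**Illustration of size**

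Inputs from the Sample size section: SD 2.5, target difference 2 points, two-sided 5% test, 80% power, 26 analysed per arm per disease group.

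The plan's own figure reproduces. A two-sample t-test with effect size 2/2.5 = 0.8 needs 25.5, that is 26 per arm, with 80.7% power at 26. The total is 26 × 2 arms × 2 disease groups = 104.

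Standard error of the difference: 2.5 × √(2/26) = 0.693.

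Assumptions not found in the article: a share s of fast-track patients is rated by an informed researcher, and this shifts each such rating by b points relative to the waiting-list arm. The bias is s × b. With no true effect, the rejection rate is Φ(bias/0.693 − 1.96) + Φ(−bias/0.693 − 1.96).

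| s | b | Bias | Bias/SE | Type I error |
|---|---|---|---|---|
| 0 | any | 0 | 0 | 5% |
| 0.25 | 0.5 | 0.125 | 0.18 | 5.4% |
| 0.5 | 0.5 | 0.25 | 0.36 | 6.5% |
| 1 | 0.5 | 0.5 | 0.72 | 11.1% |
| 0.5 | 1 | 0.5 | 0.72 | 11.1% |

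A bias of 0.5 is 0.5/2 = 25% of the target difference. This uses a normal approximation without baseline adjustment.

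**The case against.** **The gap is inferred from silence.** The article does not say whether quantitative collection must be complete for the respondent or for the dyad. Visit order is operational detail, and the Randomisation section refers to a fuller account of blinding elsewhere. This stands as a limit: the article neither requires nor rules out the safe order, and the full protocol may settle it. But the article does fix two things, the timing of the BIS interview by arm and one researcher per dyad. Followed together as written, they allow disclosure at the analysis time point.

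**Separate interviews are not established at t3.** The statement reads "Where possible, carers are interviewed separately from patients" and concerns baseline. This stands too, so the point is confined to dyads that are in fact seen one after the other.

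**A reader might infer that the primary outcome is compromised.** The article does not support that. It gives no order within the dyad at t3. The only hint, from the baseline visit, has the carer approached at or after the patient's interview. With the patient first, the inflation for the primary outcome is zero.

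**A reader might infer that every fast-track dyad, or up to half the sample, is affected and that the blind fails in that arm alone.** Neither follows. No carer participation rate is given, and the absence of a BIS interview discloses waiting-list status just as its presence discloses fast track.

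**Participants are unblinded and rate themselves.** True. Blinding the researcher can remove only interviewer influence, not participants' expectations, so the gain from the fix is limited to that component.

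**Conclusion.** The point holds in a limited form. For dyads interviewed in sequence, the t3 schedule discloses allocation in either arm to the one researcher who still has to collect the second member's quantitative outcomes. Carer outcomes are exposed if the patient is first, and the primary outcome only if the carer is first.

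The article offers no basis for the size of any interviewer effect. On assumption only, a mean shift of 0 to 0.5 points across the fast-track arm corresponds to a type I error between 5% and about 11%, with about 6.5% at 0.25 points. For a shift of 0.5 points per exposed rating, the upper end requires every fast-track patient to have a participating carer who is interviewed first. It should not be read as an estimate of the bias in this trial.

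The t5 comparison carries the same weakness more generally. By then the t3 schedule has shown the researcher who has received BIS, and in the non-malignant sub-protocol t4 interviews exist only for the waiting list. The effectiveness test is at t3, so this affects how t5 is described rather than the main conclusion.

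This is a cheap improvement to conduct and reporting, not a fault that invalidates the design.

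**What to change.** 1. At t3, complete the quantitative schedules of both patient and carer, patient distress rating first, before either qualitative section. If the two are seen on different days, hold the first respondent's qualitative section until the second's quantitative schedule is done.
2. Record, before each t3 quantitative schedule, whether the researcher already knew the allocation.
3. Repeat the t3 analysis without those cases as a sensitivity analysis. It drops patients or carers after randomisation, so it supports the intention-to-treat result and does not replace it.
4. Describe t5 between-arm estimates as collected unblinded.

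Cost: a re-ordered interview schedule, one extra field on the record form and one extra analysis. Sample size and staffing do not change. The downside is an occasional short second contact for the qualitative section.
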